### Plans to allow access to the full protocol, participant-level data and statistical code {31c}

No later than 3 years after the collection of the 1-year follow-up interviews, we will deliver a completely deidentified data set to an appropriate data archive for sharing purposes.

### Composition of the data monitoring committee, its role and reporting structure {21a}

The protocol will not have a fixed data monitoring committee because this trial has a short duration and known minimal risks. However, the Brazilian Ministry of Health may perform an audit and have experts in any field (e.g., education, psychology, trial methodology and statistics) review our protocol at any time.

### Adverse event reporting and harms {22}

There are no reports of adverse effects of the intervention in the literature. The supervision that teachers will provide throughout the intervention is also focused on discussing the possible negative effects of the game for children to prevent adverse effects. According to the Brazilian Research Ethics Committee, for people who accept to participate and sign the consent terms are guaranteed treatment for adverse effects in the next 5 years. If the participants report adverse effects of unintended consequences of the intervention, they will be assisted in the treatment by the Ministry of Health’s intervention implementation team.

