## Trial design {8}

A cluster-randomized controlled superiority trial will be performed in 30 schools in three cities (15 controls and 15 in the experimental group), with a total of 3800 children participating in the test (1900 in the control group and 1900 in the intervention group). This study is a randomized controlled trial with two parallel groups (intervention and control) of students aged 6 to 10 years and enrolled in the first to fourth year of elementary education in public schools in the cities of Fortaleza, Eusébio and São Paulo, which are located in the states of Ceará and São Paulo. The ratio of intended numbers of participants in each of the comparison groups is 1:1. The control group receives treatment as usual in Brazil, i.e., no behavioural intervention at the school.

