**Intervention**							
Elos 2.0 Programme	N	Trained teachers	480–2400			X	
Teacher supervision	N	Trained supervisor	120			X	
Supervisor supervision	N	Study coordinator	240			X	

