**Assessments**							
Teacher training	N	Interviewer	10		X		X
Bullying	N	Interviewer	15		X		X
Field checklist	N	Trained supervisor	5			X	
Fidelity	N	Trained supervisor	5			X	
Language and math	N	Interviewer	20		X		X
School observation	N	Interviewer	20		X		X
Teachers protocol	N	Interviewer	15		X		X
Game register	N	Trained supervisor	5			X	
SDQ	N	Trained teacher with mediation of a trained interviewer	15		X		X
STRS	N	Trained teacher with mediation of a trained interviewer	15		X		X
TOCA-C	N	Trained teacher with mediation of a trained interviewer	15		X		X

^a^Case report form

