### Procedure for unblinding if needed {17b}

Not applicable. This trial does not have the potential to harm or other relevant conditions that necessitate an unblinding protocol prevention.

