### Data management {19}

In the Elos 2.0 Programme, all data from the Elos 2.0 Programme will be entered in two stages: (1) interviewers will enter documents in the proper form and (2) all of the data will be entered electronically. These entries may be done at the participating site where the data was originated. Original study forms will be entered and kept on file at the participating site. A subset will be requested later for quality control. When a form is selected for review, the participating site staff will pull that form, copy it and send the copy to the study supervisor for re-entry. Participant files will be stored in numerical order in a secure and accessible place and manner. All forms related to study data will be kept in locked cabinets and access to the study data will be restricted to the study supervisor and assigned data management member staff. Participant files will be maintained in storage for three years after completion of the study. Errors will be detected by the study supervisor and data management member staff who are assigned to detect missing data or specific errors in the data.

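### Adverse effects are actively looked for only in intervention schools, and the stated file retention ends before the five-year treatment guarantee

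*Protocol article*

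**What the plan says.** **Harms.** The section on adverse event reporting and harms {22} gives two routes. The first is discussion during supervision: "The supervision that teachers will provide throughout the intervention is also focused on discussing the possible negative effects of the game for children". Its stated aim is prevention. The second is participants' own reports: "If the participants report adverse effects of unintended consequences of the intervention, they will be assisted in the treatment".

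**Where supervision sits.** In the participant timeline {13}, "Teacher supervision" is a row of the intervention block, at T1 only. On the comparator, the trial design section {8} says: "The control group receives treatment as usual in Brazil, i.e., no behavioural intervention at the school".

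**Other measures.** The assessments block of the same timeline lists a bullying measure ("Bullying N Interviewer") and the SDQ, both at time 0 and T2, with no restriction to one arm. The statistical methods section {20a} specifies four regressions, all on TOCA scores.

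**Records.** The harms section says that those who consent are "guaranteed treatment for adverse effects in the next 5 years". It does not say when the five years begin. The data management section {19} says: "Participant files will be maintained in storage for three years after completion of the study". The confidentiality section {27} stores consent forms and identity-link lists apart from the coded study records and gives no retention period for them.

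**The concern.** A harms comparison needs events to be sought in the same way in both arms. Here the active search is part of the treatment package. A supervisor asking about the game will hear of problems in intervention schools; nobody has the corresponding conversation in control schools. A difference in reports would then partly reflect who was asked, and an absence of reports from control schools would tell us little.

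This matters because the programme is meant for national dissemination and participation is mandatory for pupils in intervention schools. The trial should be able to say something about unwanted effects, and the measures that would allow it are already in the schedule without that role.

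The records point is separate. If someone seeks treatment under the guarantee after the stated storage period, the documents that show participation and exposure may no longer be held.

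**Working it through.** **1. Ascertainment by arm**

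| Route | Intervention schools (15) | Control schools (15) |
|---|---|---|
| Discussion in supervision {22}, intervention block of {13} | Yes, during T1 | No; no behavioural intervention {8} |
| Participant report {22} | Possible, passive | Worded for consequences of the intervention, so hardly applicable |
| TOCA-C, time 0 and T2 | Yes | Yes (the abstract names control and experimental classes) |
| SDQ and bullying, time 0 and T2 {13} | Scheduled | Scheduled; no restriction by arm is stated |

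The first two rows are the only ones in the harms section, and both lean to one arm. The last two rows could support a between-arm comparison. TOCA-C is analysed for effectiveness only. SDQ and bullying are given no role in assessing unintended effects.

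**2. Retention against guarantee**

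Inputs: recruitment began March 2019 and estimated completion is November 2020 (trial status); retention is 36 months from completion {19}; the guarantee is 60 months from an unstated start {22}.

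Let L be the number of months from the start of the guarantee to study completion. Then

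gap = 60 − (L + 36) = 24 − L months.

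| Start of guarantee | Completion | L | Guarantee ends | Files kept to | Gap |
|---|---|---|---|---|---|
| Consent, March 2019 | November 2020 | 20 | March 2024 | November 2023 | 4 months |
| Consent, December 2019 (assumed) | November 2020 | 11 | December 2024 | November 2023 | 13 months |
| Completion, November 2020 | November 2020 | 0 | November 2025 | November 2023 | 24 months |
| Consent, March 2019 | November 2019 (assumed) | 8 | March 2024 | November 2022 | 16 months |

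The last row is included because the abstract places both assessments in the same year, so completion before November 2020 is conceivable. The guarantee ends after the files in all four rows.

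The gap is not simply 5 − 3 = 2 years, because the two periods may start at different times. It would vanish only if L reached 24 months. For a March 2019 consent that means completion in March 2021 or later.

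**The case against.** Several stronger readings are tempting, and the document does not support them.

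- **That harm cannot be compared between arms at all.** A reader might infer this from the harms section alone. TOCA-C is completed in both arms before and after the intervention, and SDQ and bullying appear to be as well. What cannot be compared fairly is reported adverse events.
- **That supervision is the only route.** Participant report is a second one, though passive and tied to the intervention.
- **That late claims cannot be traced.** The protocol does not say that files are destroyed after three years, gives no retention period for consent forms or link lists, and does not make treatment depend on retrieving a trial file. The most one can say is that records may be missing.
- **That the protocol contradicts itself on risk.** The section on unblinding {17b} contains the words "This trial does not have the potential to harm", but the sentence continues and is there to explain why no unblinding procedure is needed. The data monitoring section speaks of minimal risks. This is a matter of wording. So is the phrase that has teachers providing the supervision, where the timeline assigns it to a trained supervisor. Neither is part of the point.

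It can also be argued that a journal article may leave the analysis of secondary measures to the full protocol or analysis plan, that the game has safeguards (every team can win and losing teams are not named), and that nothing here touches the primary analysis. These arguments stand, and they limit the weight of the point. They do not remove the one-sided search in the harms section, and they do not reconcile the two stated periods.

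**Conclusion.** The point holds in limited form. Active search for adverse effects exists in 15 of 30 schools, all in one arm, so adverse-event reports cannot be compared fairly between arms. Measures that would permit a comparison are scheduled but not assigned to it. This rests on reading the assessments schedule as applying to both arms, which the text suggests but does not state for SDQ and bullying. Such a comparison would also be imperfect for the SDQ, because the teachers who rate it are not blinded.

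The stated retention ends 4 to 24 months before the guarantee, taking November 2020 as completion and a guarantee that starts between March 2019 and completion. The range depends on an undefined start and an estimated completion date.

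The validity of the primary analysis is not affected. The changes are worth making because they improve participant protection and what the trial can say about harm, at little cost.

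**What to change.** 1. State in the harms section that SDQ and bullying, already scheduled at baseline and T2, will be compared between arms as outcomes for unintended effects. Label them as safety or secondary outcomes, so that they add nothing to the primary claim, and confirm that both are collected in control schools. The standard errors should respect the school, which is the randomised unit. The TOCA model as written clusters on classroom and should not be copied unchanged.
2. Reconcile the data management, confidentiality and harms sections: define when the five-year guarantee starts, state the retention period for consent forms and link lists, and keep consent, link and exposure records at least until the guarantee ends. The terms of the guarantee itself are for the sponsor and the ethics committee.

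Cost: two further analyses of data already scheduled, a few sentences of protocol text, and up to two more years of locked storage for part of the files.

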### Frequency and plans for auditing trial conduct {23}

The Brazilian Ministry of Health may audit the study at any time.

### Plans for communicating important protocol amendments to relevant parties (e.g., trial participants and ethical committees) {25}

Any amendments, including administrative amendments, will be approved by the Ethics Committee of the State Health Secretary (CAAE 01517218.2.0000.5505, CEP/UNIFESP no. 1246/2018) prior to implementation, and the health authorities will be notified in accordance with local regulations.

## Dissemination plans {31a}

All presentations and publications will protect the integrity of the major objectives of the study. Data that break the blinding will not be presented prior to the release of the main results. The study results will be released to the participants and the general community.

### Reproducible research {31b}

This programme is the property of the Brazilian Ministry of Health, which will be responsible for its large-scale dissemination.

## Discussion

This article presents a randomized controlled trial of the Elos 2.0 Programme to evaluate its effectiveness in reducing problem behaviours (e.g., disruptiveness, aggressiveness and shyness) and promoting social skills in the school context. This school-based prevention programme for children between 6 and 10 years of age is based on the GBG. Longitudinal studies showed that the GBG is a “behavioural vaccine” against future risk behaviours [10]. For example, several studies reported that participation in GBG resulted in a lower risk of substance abuse and dependence [12, 51] and decreased frequency of delinquency, juvenile violence and other behavioural disorders among participants [17, 52].

Despite these associations of the problem behaviours in school-age with a wide range of adverse psychosocial outcomes (e.g., crime, substance use and mental health) and the burden that it generates for caregivers and teachers, the mental health of children is neglected, especially in low- and middle-income countries (LMICs) [2]. Prevention programmes, such as the Elos 2.0 Programme, that may be adapted and tested for effectiveness are necessary, particularly in LMICs, where a tremendous gap remains between needs and the available resources [53].

### Strengths and weaknesses

This randomized trial will be performed in a representative sample of public school students in Brazil. We highlight that the randomization will be performed at the school level to ensure that there is no contamination, which can occur when the randomization is performed at the level of the classrooms within the school.

There are several limitations. For example, the intervention will not be repeated if a child is absent, but this fact is a limitation of prevention intervention designs in general [54]. We will be unable to directly evaluate children’s behaviour due to the high cost of these observations. However, the most common method used to evaluate children’s behaviour and functioning at school is the use of rating scales completed by teachers. Teachers’ ratings are predicted by the student’s gender, race/ethnicity, academic performance, disciplinary incidents, the teacher’s gender, student-teacher gender interaction, teacher professional development in behaviour screening and classroom academic performance [55].

### Trial status

 Protocol version = 1

Date of register = February 2019

Date recruitment began = March 2019

Estimate completion date = November 2020

## Abbreviations

GBG: Good Behavioural Game
INEP: National Institute for Educational Studies and Research “Anísio Teixeira”
REBEC: Registry of Clinical Trials of the Ministry of Health
